### Data analysis

#### Statistics

Interval scaled variates will be summarized with means and standard deviations (SD) or medians and interquartile ranges where appropriate. Dichotomous variates will be described as ratios and percentages.

#### Univariate analysis

T-tests will be used to compare means between groups and chi-squared tests to compare dichotomous variables.

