### Investigations

In case the patients with refractory neurogenic LUTD fulfill the study inclusion criteria following neuro-urological evaluation (bladder diary for at least 3 days, urinalysis, urodynamic investigation, urethro-cystoscopy and bladder washing cystology, Qualiveen questionnaire
[12], FSFI
[10]/IIEF
[11], they are included after providing written informed consent. The Figure 
1 gives an overview of the procedures that the patients will undergo during the course of the study. After minimally invasive bilateral tined lead placement into the sacral foramina S3 and/or S4 (stage one), patients undergo prolonged SNM testing for 3–6 weeks completing a bladder diary to assess the response to treatment. In accordance with the literature
[5,6], an improvement of at least 50% in the key bladder diary variables (i.e. number of voids and/or number of leakages, post void residual) compared to the baseline values is considered a positive test and an indication for neuromodulator implantation. At the end of the test phase, the patients have a neuro-urological re-evaluation (bladder diary for at least 3 days, urinalysis, urodynamic investigation, Qualiveen questionnaire
[12], FSFI
[10]/IIEF
[11]). In case of negative prolonged SNM testing, the tined leads are explanted. In case of successful prolonged SNM testing, the neuromodulator is generally implanted in the upper buttock (rarely in the anterior abdominal wall) (stage two). After neuromodulator implantation, each patient has a 2 months phase when the neuromodulator is turned ON using sub-sensory threshold stimulation (SNM optimization phase) to optimize the effectiveness of neuromodulation by determining the most effective stimulation parameters (choice of stimulation electrodes, intensity of stimulation) for each patient. At the end of the SNM optimization phase, patients are randomized in a double-blind parallel design to SNM ON or OFF. During an outpatient visit, neuromodulation parameters and bladder diary parameters are checked and the neuromodulator is turned ON or OFF by an investigator not involved in assessment of the clinical outcome. Considering that sub-sensory stimulation is used for SNM, the patients do not feel if the stimulation is ON or OFF. At the end of the 2 months double-blind SNM phase, the patients have a neuro-urological re-evaluation (bladder diary for at least 3 days, urinalysis, urodynamic investigation, Qualiveen questionnaire
[12], FSFI
[10]/IIEF

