#### Multivariate analysis

To adjust for unequal distribution of parameters at baseline, multivariate regression models, linear models in case of an interval scaled outcome and logistic regression in case of a dichotomous outcome will be performed.

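### Urodynamic and questionnaire outcomes: the named comparison is a t-test, and regression is introduced only to correct baseline imbalance, which gives up precision that pre-specified ANCOVA would keep

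*Protocol article*

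**What the plan says.** The Protocol article, under Univariate analysis, names the between-group tests: "T-tests will be used to compare means between groups", with chi-squared tests for dichotomous outcomes. It does not say whether the t-test is applied to end values or to changes from baseline.

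Under Multivariate analysis it continues: "To adjust for unequal distribution of parameters at baseline, multivariate regression models, linear models in case of an interval scaled outcome", with logistic regression for dichotomous outcomes. Correcting imbalance is the only purpose stated. No covariate is named, and neither section says which analysis is the main one.

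The Investigations section gives the measurement times:
- **Study entry:** "bladder diary for at least 3 days, urinalysis, urodynamic investigation, urethro-cystoscopy and bladder washing cystology, Qualiveen questionnaire", together with FSFI/IIEF.
- **End of the test phase, before implantation and randomisation:** "At the end of the test phase, the patients have a neuro-urological re-evaluation", again with urodynamics and both sets of questionnaires.
- **Randomisation visit:** "During an outpatient visit, neuromodulation parameters and bladder diary parameters are checked". Urodynamics and questionnaires are not mentioned here.
- **Outcome:** "At the end of the 2 months double-blind SNM phase, the patients have a neuro-urological re-evaluation", with the same measures.

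The Study design section stratifies randomisation by three diagnosis groups: overactive symptoms, retention, and the combination.

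**The concern.** In a randomised trial, any difference between arms at baseline is due to chance. The main reason to adjust for a baseline value is that it predicts the outcome, so adjusting removes between-patient variation from the error term. That gain is there whether or not the arms happen to differ. A plan that brings in regression to repair imbalance gives the weaker reason, and it leaves the role of the adjusted result dependent on how the baseline table turns out.

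It matters here because the trial is small and pools patients with overactive symptoms, retention or both, who can be expected to differ widely in capacity, residual volume and flow. A t-test on end values leaves that variation in the comparison. Having two analyses with no stated order also leaves room to choose between them after the results are known.

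**Working it through.** **Inputs from the article (Determination of sample size).** Success rates 0.50 and 0.15, type I error 0.05, power 0.80, 27 per group, 30 per group with drop-outs. **Assumed:** correlation r between baseline and end value of 0.3, 0.5 and 0.7.

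**1. The article's own figure.** With pooled variance, two-sided test, no continuity correction and mean rate 0.325:

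n = [1.960 × √(2 × 0.325 × 0.675) + 0.8416 × √(0.50 × 0.50 + 0.15 × 0.85)]² / 0.35²
= (1.298 + 0.517)² / 0.1225 = 26.9, so 27 per group.

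The stated 27 is reproduced, with power 80.2%. It concerns the binary primary outcome and is not affected by this point. The article gives no calculation for the continuous secondary outcomes.

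**2. Detectable difference at 27 per group, 80% power (normal approximation).**
- t-test on end values: (1.960 + 0.8416) × √(2/27) = 2.8016 × 0.2722 = 0.76 SD.
- ANCOVA: multiply by √(1 − r²).
- t-test on change scores (equal variance at both times): multiply by √(2(1 − r)).

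| Assumed r | ANCOVA variance factor 1 − r² | Change-score variance factor 2(1 − r) | Detectable, t-test on end values | Detectable, t-test on changes | Detectable, ANCOVA |
|---|---|---|---|---|---|
| 0.3 | 0.91 | 1.40 | 0.76 SD | 0.90 SD | 0.73 SD |
| 0.5 | 0.75 | 1.00 | 0.76 SD | 0.76 SD | 0.66 SD |
| 0.7 | 0.51 | 0.60 | 0.76 SD | 0.59 SD | 0.54 SD |

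Since 2(1 − r) − (1 − r²) = (1 − r)², which is never negative, change scores are never more precise than ANCOVA under these assumptions.

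**3. Equivalent t-test sample size.** 27/(1 − r²) gives 29.7, 36.0 and 52.9, that is 30, 36 and 53 per group.

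**4. Power for a difference of 0.5 SD.** 45% by t-test on end values; 49%, 56% and 73% by ANCOVA.

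**5. Simulation (40,000 runs, 27 per group, normal data, own baseline as the only covariate).** For a true difference of 0.76 SD and for no difference:

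| Strategy | Power, r = 0.3 / 0.5 / 0.7 | Type I error, r = 0.3 / 0.5 / 0.7 |
|---|---|---|
| t-test | 79% / 79% / 79% | 5.0% / 4.9% / 4.8% |
| ANCOVA always | 82% / 88% / 97% | 4.8% / 4.9% / 5.0% |
| ANCOVA only if baseline differs at p < 0.05 | 79% / 79% / 80% | 4.8% / 4.3% / 3.5% |
| Smaller of the two p-values | 84% / 90% / 97% | 6.3% / 7.2% / 8.1% |

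The last two rows show what an unfixed order could lead to. The article states neither rule.

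**The case against.** The strongest reply is that the article does plan baseline adjustment. Its Multivariate analysis section says linear models will be performed for interval-scaled outcomes, and a linear model containing the outcome's own baseline is an ANCOVA. The section gives a purpose and no trigger, so a rule of adjusting only after a significant baseline test is something a reader might infer but cannot find in the text. This stands. It would be wrong to say that the trial ignores baseline values, and the third row of the simulation illustrates a risk, not the plan.

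A second reply is that a condensed article may leave covariate lists to an analysis plan that is not shown. This also stands as far as it goes: an unnamed covariate alone would not be a finding. What remains is what the article does state, namely a t-test as the between-group comparison of means and imbalance as the reason for regression.

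Third, the t-test might be meant for change scores, which would use the baseline. The text leaves this open, but change scores do no better than ANCOVA at any correlation and do worse than end values below r = 0.5.

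Fourth, the higher correlations may be optimistic. Entry and outcome are separated by 3–6 weeks of testing, 2 months of optimisation and 2 months of blinded stimulation, and only patients who responded to testing are randomised. At r = 0.3 the gain is small, 0.76 to 0.73 SD, which is why the range starts there.

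Finally, not every secondary outcome has a usable baseline. No pre-randomisation measurement is described for costs, and volume at overactivity, its pressure amplitude and leak point pressure are recorded only if overactivity is present. The point is limited accordingly.

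**Conclusion.** The point holds for interval-scaled urodynamic and questionnaire outcomes that have a pre-randomisation value. Pre-specified ANCOVA is a better main analysis than a t-test accompanied by regression aimed at imbalance with the order left open. The gain runs from slight (0.73 SD against 0.76 SD at r = 0.3) to substantial (0.54 SD at r = 0.7), and it rests on assumed correlations and the planned 27 per group. The 27 per group applies to measures taken in all patients. FSFI and IIEF, if given by sex, have fewer.

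A reader might infer that the t-test is biased or inflates the error rate. It does not: its simulated type I error is 4.8–5.0%. The 6.3–8.1% arises only if the smaller of two p-values is reported, and nothing in the article proposes that. The loss is one of precision and is confined to secondary outcomes.

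**What to change.** Amend the Univariate and Multivariate analysis sections, or the analysis plan, before unblinding. Patients are unblinded one by one at the end of their blinded phase, so in practice the wording should be settled before any outcome is compared by arm.

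- **Main analysis:** for each interval-scaled urodynamic and questionnaire outcome with a pre-randomisation value in all patients to whom the measure applies, ANCOVA of the value at the end of the blinded phase.
- **Fixed covariates:** the study-entry value of the same measure and the three-level diagnosis stratum, included whatever the observed imbalance. The baseline must be named because there are two candidates; the end-of-test value was taken under stimulation.
- **Reporting:** adjusted mean difference with 95% CI.
- **Supportive analysis:** the t-test, stating whether it uses end values or changes.
- **Outside this rule:** costs, and measures recorded only if overactivity is present.

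The cost is wording, plus one degree of freedom for the baseline and two for the stratum: with 54 patients the error degrees of freedom fall from 52 to 49. No visit, measurement or patient is added, and the primary outcome and sample size do not change.

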#### Multivariate analysis

To adjust for unequal distribution of parameters at baseline, multivariate regression models, linear models in case of an interval scaled outcome and logistic regression in case of a dichotomous outcome will be performed.

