### Study population and recruitment

According to the inclusion and exclusion criteria (Table 
1), we will investigate patients with refractory neurogenic LUTD. The following variables will be considered: gender, age, neurological disease, duration of neurological disease, previous treatment, bladder diary variables, urinalysis, urethro-cystoscopy, bladder washing cytology, urodynamic investigations, and questionnaires, i.e. Female Sexual Function Index (FSFI)
[10]/International Index of Erectile Function (IIEF)
[11] and Qualiveen
[12].

**Table 1 T1:** Inclusion and exclusion criteria for patients with refractory neurogenic lower urinary tract dysfunction (LUTD)

**Inclusion criteria**	**Exclusion criteria**
▪ Age >18 years	▪ Age <18 years
▪ Refractory neurogenic LUTD	▪ Non-neurogenic LUTD
▪ Urgency frequency syndrome and/or urgency incontinence refractory to antimuscarinics (pharmacotherapy for at least 4 weeks with at least 2 antimuscarinics)	▪ Botulinum toxin injections into the detrusor and/or urethral sphincter in the last 6 months
▪ Chronic urinary retention refractory to alpha-blocker (pharmacotherapy with an alpha-blocker for at least 4 weeks)	▪ Pregnancy or breast feeding
▪ Combination of urgency frequency syndrome and/or urgency incontinence refractory to antimuscarinics (pharmacotherapy for at least 4 weeks with at least 2 antimuscarinics) and chronic urinary retention refractory to alpha-blocker (pharmacotherapy with an alpha-blocker for at least 4 weeks)	▪ Individuals especially in need of protection (according to Research with Human Subjects published by the Swiss Academy of Medical Sciences ( http://www.samw.ch/en/News/News.html))
▪ Written informed consent	▪ No written informed consent

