### Determination of sample size

We are planning a study of independent cases and controls with 1 control per case. Prior data indicate that the (spontaneous) success rate among controls is 0.15. If the true success rate for experimental subjects (SNM ON) is at least 0.5, we will need to study 27 experimental subjects (SNM ON) and 27 control subjects (SNM OFF) to be able to reject the null hypothesis that the failure rates for experimental (SNM ON) and control subjects (SNM OFF) are equal with probability (power) 0.8. The type I error probability associated with this test of this null hypothesis is 0.05. Taking into account potential drop-outs, we will include 30 patients per group.

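### The regression is justified only by chance baseline imbalance, which ignores prognosis and the three randomisation strata; planned power is not undercut, but power is forgone and the adjusted model depends on the data

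*Protocol article*

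**What the plan says.** The primary outcome (Study outcome measures) is binary: success is an improvement of at least 50% in the key diary variables for the patient's diagnosis. Randomisation is 1:1 and takes account of three diagnosis strata (Study design).

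Two analyses apply to that outcome. Univariate analysis plans "chi-squared tests to compare dichotomous variables". Multivariate analysis adds linear or logistic models, and its only stated reason is "To adjust for unequal distribution of parameters at baseline, multivariate regression models". That section names no covariate, gives no rule for judging inequality and does not mention the strata.

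The baseline variables are listed under Study population and recruitment: "The following variables will be considered: gender, age, neurological disease, duration of neurological disease, previous treatment, bladder diary variables", followed by urinalysis, cystoscopy, cytology, urodynamics and questionnaires.

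Determination of sample size uses an unadjusted comparison of two success rates: "Prior data indicate that the (spontaneous) success rate among controls is 0.15", and "If the true success rate for experimental subjects (SNM ON) is at least 0.5" for the active arm.

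**The concern.** Randomisation makes baseline differences chance differences, so an observed inequality says nothing about whether a variable predicts success. A model driven by inequality can include an irrelevant variable that happens to differ and leave out a strong predictor that happens to be balanced. It also makes the model's content depend on the data. The stratification factors belong in the analysis because they shaped the allocation, yet neither analysis section uses them.

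Three things are at stake. Precision that a prespecified covariate could bring is given up. The chi-squared and adjusted results can differ for the same binary outcome. And there is room for judgement about the covariates once the data are seen.

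**Working it through.** **1. The plan's own figure.** Inputs from Determination of sample size: success 0.15 (OFF) and 0.50 (ON), type I error 0.05, power 0.80. Sidedness is not stated; two-sided is assumed. The mean rate is 0.325.

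n = [1.960 × √(2 × 0.325 × 0.675) + 0.842 × √(0.15 × 0.85 + 0.50 × 0.50)]² / 0.35²

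= (1.298 + 0.517)² / 0.1225 = 26.9, so 27 per arm.

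Power at 27 = Φ[(0.35 × √27 − 1.298) / 0.614] = Φ(0.847) = 0.802. The exact power of the uncorrected chi-squared test is 0.820 at 27 per arm and 0.847 at 30. The stated number therefore fits an unadjusted test, and that test delivers the planned power.

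**2. How often something looks unequal.** For k independent variables and a 0.05 threshold (an assumption; the article gives none), the chance of at least one is 1 − 0.95^k. This is 23% for k = 5, 40% for k = 10 and 43% for k = 11. A given prognostic variable is picked up only about 5% of the time.

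**3. Effect on the binary primary outcome.** Simulated trials, 27 per arm, marginal rates 0.15 and 0.50, 2,000 trials per setting. Assumptions not in the article: six candidate covariates, one of them prognostic, and selection at baseline p < 0.05.

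| Log-odds per SD of the prognostic covariate | Chi-squared | Logistic, imbalance-selected | Logistic, prespecified | Forgone (prespecified − selected) | Chi-squared and selected model disagree |
|---|---|---|---|---|---|
| 0 | 0.806 | 0.796 | 0.810 | 1.4 points | 2.8% |
| 1 | 0.806 | 0.804 | 0.864 | 6.0 points | 3.0% |
| 1.5 | 0.812 | 0.818 | 0.902 | 8.4 points | 3.6% |
| 2 | 0.812 | 0.827 | 0.947 | 12.0 points | 4.1% |

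The standard error of one power figure is about √(0.8 × 0.2 / 2000) = 0.9 points, so the first row is close to no difference.

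**4. Type I error if either result may be claimed.** With a common success rate of 0.15 or 0.30, chi-squared alone rejects in 5.4 to 6.0% of trials, and either-or in 6.0 to 7.2%. Within a setting the increase is 0.4 to 1.2 points (for example 7.2 − 6.0 = 1.2). The prespecified logistic model rejects in 5.1 to 6.6%, so it is itself slightly liberal at this size and a little of its gain in power may come from that.

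**5. Accounting for the three strata.** Cochran-Mantel-Haenszel (CMH) test, assuming 9 patients per arm in each stratum:

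| Log-odds step between strata | Chi-squared | CMH |
|---|---|---|
| 0 | 0.820 | 0.806 |
| 0.5 | 0.823 | 0.819 |
| 1 | 0.833 | 0.851 |
| 1.5 | 0.848 | 0.890 |
| 2 | 0.861 | 0.926 |

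The cost is 1.4 points if the strata carry no prognostic information. The gain is 6.5 points at the strongest step.

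**6. Room for covariates.** Expected successes: 27 × 0.50 + 27 × 0.15 = 13.5 + 4.05 = 17.55. A logistic model with about 18 events can carry few terms.

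**The case against.** The section on multivariate analysis states a purpose. It describes no screening test or threshold, and the baseline list sits under study population and is not labelled a covariate pool. Selection by imbalance is the natural reading, but it is not literal wording. That much stands, and it is why the thresholds above are marked as assumptions. A later covariate list would still have to replace the stated rationale, because that rationale is the only one given and it is the wrong one.

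A reader might also object that no result is named as primary. That is largely a matter a condensed article may leave to the full protocol or analysis plan. The sample size, built on unadjusted proportions, points to chi-squared as the main test, though the text does not say so. This silence is not counted as an error in its own right.

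The either-or error rate applies only if the team claims whichever result is significant. Nothing in the article says it will.

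**Conclusion.** The stated basis for adjustment is poor and should be replaced. The practical size is moderate: 0 to about 12 points of power forgone on the binary primary outcome, disagreement in about 3 to 4% of trials with an effect, and about one point of type I error if either result could be claimed. These figures rest on assumed prognostic strengths, six candidate covariates and selection at p < 0.05, none of which the article gives.

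A reader might infer that the plan loses power against its own target. It does not: 27 per arm gives 0.802 for the unadjusted test, and the imbalance-driven model stays at about 0.80 or above, within simulation error. Larger contrasts can be produced for an interval-scaled outcome. With 12 candidates, two of them explaining half the variance, selection at p < 0.10 and an effect of 0.8 residual SD, power is 51% with imbalance selection, 53% unadjusted and 81% prespecified, with 15% disagreement. Those inputs are not in the article, and the outcome type is not that of the primary endpoint, so they do not measure the harm here.

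**What to change.** Make three wording changes in the data analysis section.

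- Delete baseline inequality as the reason for regression.
- Analyse the primary outcome with one named analysis that accounts for the three randomisation strata, for example a CMH test stratified by diagnosis.
- Fix the supporting logistic model now as treatment, diagnosis stratum and the baseline value of the key diary variable, whatever balance is observed. State which variable that is in each stratum, because the outcome definition uses different ones.

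A penalised likelihood is optional, given about 18 expected successes.

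The cost is about one point of power if the strata are not prognostic (0.806 against 0.820), and covariates can no longer be chosen later. The baseline diary is already collected, and the sample size stays as planned.

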### Ethics and dissemination

This trial will be performed in accordance with the World Medical Association Declaration of Helsinki
[13], the guidelines for Good Clinical Practice
[14] and the guidelines of the Swiss Academy of Medical Sciences
[15]. Handling of all personal data will strictly comply with the federal law of data protection in Switzerland
[16]. The trial has been registred at clinicaltrials.gov (www.clinicaltrials.gov/ct2/show/NCT02165774).

## Discussion

First-line treatment for neurogenic LUTD includes antimuscarinics and some form of catheterization if necessary, preferably intermittent self-catheterization
[17]. However, the treatment effect is often unsatisfactory, so that other options have to be considered, including onabotulinumtoxinA injections into the detrusor
[18] or more invasive procedures such as bladder augmentation or urinary diversions. Thus, it is of utmost importance to know whether the minimally invasive and completely reversible SNM, a well established and widely accepted therapy for refractory non-neurogenic LUTD, would be a valuable treatment option for patients with refractory neurogenic LUTD. In addition, SNM may enable voiding without intermittent catheterization, the standard technique for chronic neurogenic urinary retention today. As a significant number of patients cannot perform this technique due to the underlying neurological disorder, SNM may not only prevent major surgery but also life-long treatment with indwelling catheters, which are related to significant long-term complications.

Assessing efficacy and safety of SNM for neurogenic LUTD, it is essential to be aware of the fact that these patients usually have undergone multiple failed previous treatments. In the case that SNM is also effective in the neurological population, this would have major implications for daily practice and would completely revolutionize the management of neurogenic LUTD.

This trial is multidisciplinary and will significantly influence all involved disciplines, i.e. neuro-urology, urology, and neurology. Especially in neurology, this project will increase the awareness of LUTD in neurological disorders and the related effective treatment options including SNM.

